**Methods:**

This study will use a randomized controlled design to evaluate the efficacy of the Parent Child Interaction Therapy - Toddler intervention for children aged 14–24 months with disruptive behaviors. Ninety toddlers with parent-reported disruptive behavior will be randomly allocated to either Parent Child Interaction Therapy - Toddler, Circle of Security– Parenting™ or a waitlist control group. Key parenting capacity outcome variables will include positive and negative parenting, parenting sensitivity, parental sense of competence in managing negative toddler emotions, parent sense of caregiving helplessness, parent mentalizing about the child, parent emotion regulation, child abuse potential and parental stress. Key outcome variables for children will include child social-emotional functioning (initiative, relationship functioning, self-regulation), child emotion regulation, child attachment security, and child behavior.

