### Procedure

#### Recruitment

After being referred to the KTC, families will be informed about the research study and will undergo a clinical intake procedure including (i) an initial phone-based intake interview conducted by an Intake Officer, (ii) a 20-min in-depth phone-based intake assessment conducted by a member of the clinical research team, and, (iii) for complex cases, case review at a weekly multidisciplinary team meeting. A member of the clinical research team will then phone the families who appear suitable for the KTC service to schedule an initial face-to-face clinical assessment session. To be included in the study, the family must have a child aged 14–24 months, a referral from a health professional, and the parent must give a positive response to one or both of two screening questions (‘Do you have concerns about your child’s behavior?’ and/or ‘Do you have difficulties managing your child’s behavior?’). No other screening questions or measures will be used to assess eligibility, however families will be excluded from the study if there is evidence (in the information obtained in the referral or intake assessment) of severe parental depression with suicidality or other serious mental health conditions causing significant impairment in cognition or behaviors (e.g., psychosis) or if they are not sufficiently proficient in speaking English to complete study measures and protocols. Parents will be told that the study seeks to test different approaches to helping parents who are struggling with challenging toddler behaviour. Eligible and willing parents will provide written, informed consent to participate in the research during the first face-to-face assessment session at the KTC.

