#### Randomization

Participants who meet the study inclusion criteria will be randomly assigned to receive one of the three conditions using restricted block randomization, using block sizes of *n* = 6. This means that within each block of *n* = 6, 2 participants will be allocated to the PCIT-T condition, 2 participants will be allocated to the COS-P condition and 2 participants will be allocated to the Waitlist condition. The order will be randomized within each block. Figure 1 shows the way that participants will flow through the three assessment points for the study (Time 1, T1; Time 2, T2; Time 3; T3). Randomization will occur at the start of the first face-to-face assessment session (T1), with allocations pulled out of pre-prepared sealed envelopes, but the research team and family will not be informed of the condition to which they have been allocated until after completion of the entire T1 assessment.

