#### Time 1 assessment

All participants will complete the T1 assessment, conducted over three separate sessions in a one-week period. The first T1 session will be clinic-based and will include a clinical interview (family background, presenting problems, risk assessment) followed by three video-taped observational tasks. The first observational task will be the SSP [15], an experimental procedure comprising eight three-minute intervals involving separations and reunions between the mother and the child. The SSP will be later coded for child attachment pattern (see Measures section). The second observational task will be a structured parent-child interaction involving five sequential 4-min episodes (‘free play,’ ‘child-led play,’ a ‘frustration situation’ (toys taken out of the room), ‘toy reunion’ (toys returned to the room), and ‘clean up’), each preceded by standardised instructions provided to the parent from behind a one-way mirror through a wireless headset/bug-in-the-ear microphone. The parent-child interaction will later be coded for parent behaviour and sensitivity (see Measures section). The third observational task will be a ‘child frustration’ task [51] in which a large, locked Perspex box containing an unreachable colourful toy with flashing lights will be positioned in the centre of the room. The child will be left for 5 min to interact with the locked box while the parent completes a pen-and-paper questionnaire in the same room. Parents will be told to respond to the child’s advances as though they were needing to complete an urgent task before rejoining their child. The ‘child frustration’ task will later be coded for child emotion regulation maturity (see Measures section). The second T1 assessment session, also clinic based, will comprise the remainder of the clinical interview if not finished at the first session. The third T1 assessment session will be a 60–90-min home visit in which a research assistant will observe and video-tape the parent and child interacting in their natural environment in a series of semi-structured tasks including free play (with and without toys), reading a book, two divided attention tasks (parent completes a questionnaire and parent speaks with the researcher), a snack/mealtime, and playing a game with the researcher. The video-taped home visit will be later coded for infant attachment security (see Measures section). During the home visit, the parent will also be asked to provide a speech sample in which the parent will answer an open ended question, “What is your child like?” The speech sample will be audio-taped and transcribed verbatim, and then coded for parent mentalizing about the child, operationalized as mind-mindedness (see Measures section).

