#### T2 and T3 assessments

Following the completion of the T1 assessment, participants will commence the treatment condition to which they have been allocated (details of interventions provided below). Participants allocated to an active intervention group (PCIT-T or COS-P) will commence treatment as soon as possible, after which they will complete the T2 assessment (immediately post-treatment, i.e., 8 weeks after the T1 assessment), and the T3 assessment (4-months after the T2 assessment). Participants allocated to the Waitlist group will complete the T2 assessment at the end of the 8-week waiting period. The T2 and T3 assessments will be identical to that of the T1 assessment, except that the SSP will not be repeated at T2.

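### The envelope is drawn up to a week before the allocation is used, so families lost during the T1 assessment become randomized losses

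*Protocol article*

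**What the plan says.** The Randomization section of the protocol article sets the time of the draw: "Randomization will occur at the start of the first face-to-face assessment session (T1), with allocations pulled out of pre-prepared sealed envelopes". The same sentence adds that the research team and the family "will not be informed of the condition to which they have been allocated until after completion of the entire T1 assessment".

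The Time 1 assessment section describes T1 as "conducted over three separate sessions in a one-week period": a clinic session with interview and filmed tasks, a second clinic session, and a home visit. Under T2 and T3 assessments, treatment follows T1: "Following the completion of the T1 assessment, participants will commence the treatment condition to which they have been allocated".

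The abstract counts the sample at the point of allocation: "Ninety toddlers with parent-reported disruptive behavior will be randomly allocated to either". The Statistical analysis section commits to intention-to-treat analysis in the assigned arm, with group means estimated from all observed data.

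**The concern.** The draw and the first use of its result are separated by the whole baseline assessment, up to a week. No stated procedure in that week needs the allocation, and the article gives no reason for drawing early.

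The separation has two consequences. First, a family that attends the first session but does not finish T1 is already randomized. It uses one of the ninety places and belongs to the intention-to-treat set, yet may contribute a partial baseline and nothing at T2 or T3. Had the draw come after T1, the same family would simply not have entered the randomized sample. Second, a drawn allocation exists throughout baseline data collection and has to be kept hidden. A later draw removes that task.

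At stake are the number of randomized families with usable outcomes and the cleanness of the intention-to-treat sample. Loss during T1 is plausible: the Discussion itself lists the large number of measures as a burden on participants.

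**Working it through.** **Order of events, from the text**

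1. First T1 session begins: envelope drawn (Randomization).
2. Rest of the first session, second session and home visit, all within a week (Time 1 assessment).
3. T1 complete: allocation disclosed (Randomization).
4. Treatment or waiting period starts (T2 and T3 assessments).

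The allocation is first used at step 3 or 4. A loss during step 2 falls after randomization only because the draw is at step 1.

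**Inputs for the size**

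From Sample size and power calculations: 30 per group, difference 8.0, SD 9, alpha .05/4 = .0125, correlation between measurements .6. A two-sided test is assumed, since sidedness is not stated. The T1 loss rate is not given; I assume 0, 1 or 2 families per arm, not replaced. That is 0, 3 or 6 of 90, or 0%, 3.3% or 6.7%.

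**Reproducing the protocol's figure**

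Two-sample t-test with n per arm: noncentrality = difference / (SD × √(2/n)), df = 2n − 2, power from the noncentral t distribution.

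At n = 30: 8 / (9 × √(2/30)) = 3.443, df = 58, two-sided critical value 2.578, power 80.3%. The stated 80% is reproduced.

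**Effect of losses during T1**

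The change-score SD is 9 × √(2 × (1 − .6)) = 9 × √.8 = 8.05.

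| n per arm | Total | Power, raw SD 9 | Power, change-score SD 8.05 |
|---|---|---|---|
| 30 | 90 | 80.3% | 89.4% |
| 29 | 87 | 78.6% | 88.1% |
| 28 | 84 | 76.8% | 86.7% |

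The fall from 30 to 28 per arm is 80.3 − 76.8 = 3.5 points on the raw SD and 89.4 − 86.7 = 2.7 points on change scores. The raw-SD column is the protocol's own pairwise calculation. The change-score column is closer to the planned repeated-measures model, which includes T1, but that choice of contrast is my assumption.

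**The case against.** The strongest defence is that the present order is workable. Eligibility is settled before the draw, through referral, phone intake and team review of complex cases. The allocation is concealed during T1, so dropout in that week should be unrelated to arm, and intention-to-treat analysis keeps everyone where they were assigned. The amount lost is unknown and may be nil. The article does not bar enrolling beyond ninety, and replacement rules may well stand in a fuller document. The pairwise power figure is also conservative: on change scores, power stays above 80% even at 28 per arm, and the group-by-time test is stated to need only 48 participants. All of this stands, and it limits the point to a small one. It does not supply a reason for drawing early.

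A reader might go further and infer that the early draw leads to exclusions after randomization. The first T1 session "will include a clinical interview (family background, presenting problems, risk assessment"), and the second "will comprise the remainder of the clinical interview if not finished at the first session", so a serious parental condition could first come to light once the envelope is open. The text does not support that reading. The mental-health exclusion is tied to earlier information: "families will be excluded from the study if there is evidence (in the information obtained in the referral or intake assessment) of severe parental depression". The Recruitment section also rules out further eligibility screening. A condition first seen at T1 is therefore not a ground for exclusion, and no mental-health exclusion is planned after the draw. Whether the criterion should be wider is a separate and debatable design choice, and the content of the risk assessment is not defined.

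A reader might also infer selection bias. With the allocation hidden from team and family until T1 ends, there is no stated route by which arm could drive losses in that week.

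**Conclusion.** The point holds as a minor weakness of sequence. Drawing at the start of T1 turns any family lost in that week into a randomized loss, with no stated benefit in return. It is not an internal contradiction, and it does not bias the comparison so long as concealment holds.

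If one or two families per arm were lost in that week and not replaced, pairwise power would fall by 1.7 or 3.5 points on the protocol's raw-SD inputs, to just below the stated 80%. On change scores the fall would be 1.3 or 2.7 points, from a higher start. With no loss during T1, or with full replacement, the effect on power is zero. The figures rest on an assumed loss count, a two-sided test and equal losses across arms. Lowest severity: a cheap improvement.

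**What to change.** In the Randomization section, draw the envelope only once the T1 assessment is complete, at the moment the allocation is already disclosed. Count families lost before that as not randomized, and continue recruiting until ninety have been randomized. Leave the exclusion criterion in the Recruitment section as it is.

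This changes the time of one step. The draw moves by at most about a week, disclosure and treatment start do not move, and no procedure is added. The downside is that a few families may complete part of T1 without being randomized. For an assumed 0 to 6 replacements at three sessions each, that is at most 6 × 3 = 18 extra sessions on a planned 90 × 3 = 270, or 6.7%.

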**Fig. 1 Fig1:**
[figure not shown]
Participant flow through the study

#### Time 1 assessment

All participants will complete the T1 assessment, conducted over three separate sessions in a one-week period. The first T1 session will be clinic-based and will include a clinical interview (family background, presenting problems, risk assessment) followed by three video-taped observational tasks. The first observational task will be the SSP [15], an experimental procedure comprising eight three-minute intervals involving separations and reunions between the mother and the child. The SSP will be later coded for child attachment pattern (see Measures section). The second observational task will be a structured parent-child interaction involving five sequential 4-min episodes (‘free play,’ ‘child-led play,’ a ‘frustration situation’ (toys taken out of the room), ‘toy reunion’ (toys returned to the room), and ‘clean up’), each preceded by standardised instructions provided to the parent from behind a one-way mirror through a wireless headset/bug-in-the-ear microphone. The parent-child interaction will later be coded for parent behaviour and sensitivity (see Measures section). The third observational task will be a ‘child frustration’ task [51] in which a large, locked Perspex box containing an unreachable colourful toy with flashing lights will be positioned in the centre of the room. The child will be left for 5 min to interact with the locked box while the parent completes a pen-and-paper questionnaire in the same room. Parents will be told to respond to the child’s advances as though they were needing to complete an urgent task before rejoining their child. The ‘child frustration’ task will later be coded for child emotion regulation maturity (see Measures section). The second T1 assessment session, also clinic based, will comprise the remainder of the clinical interview if not finished at the first session. The third T1 assessment session will be a 60–90-min home visit in which a research assistant will observe and video-tape the parent and child interacting in their natural environment in a series of semi-structured tasks including free play (with and without toys), reading a book, two divided attention tasks (parent completes a questionnaire and parent speaks with the researcher), a snack/mealtime, and playing a game with the researcher. The video-taped home visit will be later coded for infant attachment security (see Measures section). During the home visit, the parent will also be asked to provide a speech sample in which the parent will answer an open ended question, “What is your child like?” The speech sample will be audio-taped and transcribed verbatim, and then coded for parent mentalizing about the child, operationalized as mind-mindedness (see Measures section).

A series of parent-report questionnaires will be provided to the parent at the first T1 assessment session to be completed at home and returned during the T2 assessment session. For those unable to complete the questionnaires in this time frame, additional opportunity to complete questionnaires is provided during the home visit if required.

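### The rule that T1 questionnaires are returned at the T2 session contradicts the one-week T1 period and the masking rule; it is probably a slip, but as written it allows post-treatment baselines for seven outcomes

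*Protocol article*

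**What the plan says.** All references are to the protocol article.

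- **Time 1 assessment, hand-out and return.** "A series of parent-report questionnaires will be provided to the parent at the first T1 assessment session", and they are "to be completed at home and returned during the T2 assessment session".
- **Time 1 assessment, fallback.** For parents who cannot manage that, "additional opportunity to complete questionnaires is provided during the home visit if required".
- **Time 1 assessment, schedule.** T1 is "conducted over three separate sessions in a one-week period", and "The third T1 assessment session will be a 60–90-min home visit".
- **Randomization.** T1, T2 and T3 are introduced as labels for the three assessment points, Time 1 to Time 3. The research team and the family "will not be informed of the condition to which they have been allocated until after completion of the entire T1 assessment".
- **T2 and T3 assessments.** Treatment begins once T1 is complete. T2 comes straight after treatment, eight weeks on from T1; for the waitlist group it comes at the end of the eight-week wait. T2 repeats the T1 battery apart from the Strange Situation Procedure.
- **Statistical analysis.** T1 scores enter a repeated-measures linear mixed model with a group-by-time interaction, Cohen's d for T1 to T2, and reliable change indices. The planned group comparisons are made at T2 and at T3.

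**The concern.** T2 is a defined term, and the return rule uses it. Read literally, a T1 form may still be with the family eight weeks after it was handed out. By then the parent knows the allocation and has finished the programme or, on the waitlist, the wait. Because T2 repeats the same questionnaires, the T1 and T2 copies of a scale could be filled in at about the same time.

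A T1 score obtained in that way is no longer a baseline. It is a post-randomization measurement, reported by a parent who is not masked. If it reflects the current state, change is understated. If the parent tries to recall how things were before treatment, the error could go either way. Each analysis that uses change from T1 would inherit it, and later analysis could not recover a baseline that was never taken.

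**Working it through.** **1. Comparing the timing statements.**

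| Statement | Section | Point in time it implies |
|---|---|---|
| Forms handed out | Time 1 assessment | First T1 session |
| Forms returned | Time 1 assessment | T2, eight weeks after T1 |
| Fallback for late completers | Time 1 assessment | Home visit, the third T1 session, within the T1 week |
| Allocation disclosed | Randomization | After all of T1 is complete |
| Treatment starts | T2 and T3 assessments | After T1 is complete |

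These cannot all hold. If the forms are part of T1, as Table 1 lists them, and they come back at T2, then T1 is not complete until T2, and neither disclosure nor treatment could happen before T2. The fallback would also fall about eight weeks before the deadline it is meant to relieve. If the return point is instead the second T1 session, every row fits.

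**2. Outcomes affected.** Table 1 lists 13 continuous outcomes: nine for parenting, and four for the child once the categorical Strange Situation classification is set aside. Seven are questionnaires completed by the parent: CTNES, CHQ, BCAP, DERS, PSI-SF, DECA and CBCL. The observational measures and the speech sample are not affected.

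**3. Reproducing the stated sample sizes.** The inputs come from Sample size and power calculations: T1 mean 24 in all groups; T2 means 13 (PCIT-T), 16 (COS-P) and 22 (waitlist); SD 9; correlation 0.6.

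- Changes are -11, -8 and -2, with mean -7. Their SD is √[(16 + 1 + 25)/3] = √14 = 3.74.
- SD of change = 9 × √(2 × (1 - 0.6)) = 8.05.
- f on change = 3.74/8.05 = 0.465. At cell level, f = 3.74/(2 × 9) = 0.208, against the stated .21.
- Noncentral F, alpha .05: 16 per group gives 80.3% power and 15 per group gives 77.3%. The stated minimum of 48 reproduces.
- Pairwise, 30 per group, difference 8.0, SD 9, alpha .05/4 = .0125: 80.3% by the noncentral t. The stated 80% reproduces.

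**4. Illustration of the effect of late forms.** Let q be the share of T1 forms, equal in every arm, that reflect the T2 state. The documents give no value for q, so it is an assumption. The planned PCIT-T versus waitlist difference in change is (24 - 13) - (24 - 22) = 11 - 2 = 9, and it becomes 9(1 - q). Interaction power is shown with the SD of change held at 8.05, which is a simplification.

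| q | Difference in change | Power, 16 per group | Power, 30 per group |
|---|---|---|---|
| 0 | 9.0 | 80% | 98% |
| 10% | 8.1 | 71% | 95% |
| 25% | 6.75 | 54% | 84% |
| 50% | 4.5 | 27% | 48% |

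**5. What does not move.** The PCIT-T versus waitlist contrast at T2 is 22 - 13 = 9 whatever q is. With complete data and separate means for each group and time, the planned contrasts at T2 and T3 rest on the T2 and T3 scores alone.

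**The case against.** The strongest reply is that no one planned this. The T1 week, the masking rule, the start of treatment and the home-visit fallback all point to return at the second T1 session. That session is clinic-based and otherwise holds only what is left of the clinical interview. This largely stands. A reader might infer that the trial intends to collect baselines after treatment, and the document as a whole does not support that. What remains is that the sentence uses a defined label, nothing in the article corrects it, and staff who followed it would accept late forms.

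The reply also limits the consequences, and these points stand:

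- The sentence sets a return point, not a completion date. A form returned at T2 may have been filled in during the first week. A reader might infer that every baseline could be late, but the text gives no share at all.
- A reader might infer that a baseline adjustment is invalidated. The Statistical analysis section plans no baseline covariate; T1 is one of the repeated outcomes.
- A reader might infer that the trial's power is compromised. The reduction by (1 - q) applies to differences in change. It does not apply to the planned contrasts at T2 and T3 with complete data, and no stated sample size is wrong.
- A reader might also object that the envelope is drawn at the start of the first T1 session, so that families who stop during the T1 week have already used a slot. Allocation stays hidden until T1 is complete, so such losses cannot depend on knowledge of the arm. The documents show no bias from this, and moving the draw would be a matter of preference.

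**Conclusion.** The point holds as an internal contradiction in an operative procedure. The return rule for the T1 questionnaires cannot be squared with the T1 schedule, the masking rule, the start of treatment or its own fallback. A slip for the second T1 session is the likeliest explanation, but the article does not say so.

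If the sentence were followed as written, the T1 values of seven of 13 continuous outcomes, including the sizing outcome, could be obtained after disclosure and after treatment or the wait. The analyses exposed are the group-by-time interaction, the T1-T2 Cohen's d and the reliable change indices. The size depends wholly on q, which is unknown: the 9-point difference in change falls to 9(1 - q) if late forms report the current state in equal shares across arms. With complete data the T2 and T3 contrasts are untouched, and the figures of 48 in total and 30 per group stand.

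**What to change.** Reconcile the passages in one place, under Time 1 assessment:

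- State that T1 questionnaires are completed, dated and collected within the one-week T1 period, at the second T1 session or at the home visit at the latest, and before allocation is disclosed.
- State that a form dated after disclosure is not used as a T1 value in the main analysis.

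The cost is a sentence or two and a completion date on each form. A few baseline questionnaires may be missing that would otherwise have arrived late; the mixed model can use the partial data from those families. No change to the sample size or to the randomization procedure is needed.
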